## Abstract

**Background:**

Dental service provision in the care home sector is poor, with little emphasis on prevention. Emerging evidence suggests that the use of Dental Care Professionals (dental therapists and dental nurses) as an alternative to dentists has the potential to improve preventive advice, the provision of care and access to services within care homes. However, robust empirical evidence from definitive trials on how to successfully implement and sustain these interventions within care homes is currently lacking. The aim of the study is to determine whether Dental Care Professionals could reduce plaque levels of dentate older adults (65 + years) residing in care homes.

**Methods:**

This protocol describes a two-arm cluster-randomised controlled trial that will be undertaken in care homes across Wales, Northern Ireland and England. In the intervention arm, the dental therapists will visit the care homes every 6 months to assess and then treat eligible residents, where necessary. All treatment will be conducted within their Scope of Practice. Dental nurses will visit the care homes every month for the first 3 months and then three-monthly afterwards to promulgate advice to improve the day-to-day prevention offered to residents by carers. The control arm will be ‘treatment as usual’.

Eligible care homes (*n* = 40) will be randomised based on a 1:1 ratio (20 intervention and 20 control), with an average of seven residents recruited in each home resulting in an estimated sample of 280. Assessments will be undertaken at baseline, 6 months and 12 months and will include a dental examination and quality of life questionnaires. Care home staff will collect weekly information on the residents’ oral health (e.g. episodes of pain and unscheduled care). The primary outcome will be a binary classification of the mean reduction in Silness-Löe Plaque Index at 6 months. A parallel process evaluation will be undertaken to explore the intervention’s acceptability and how it could be embedded in standard practice (described in a separate paper), whilst a cost-effectiveness analysis will examine the potential long-term costs and benefits of the intervention.

**Discussion:**

This trial will provide evidence on how to successfully implement and sustain a Dental Care Professional-led intervention within care homes to promote access and prevention.

**Trial registration:**

ISRCTN16332897. Registered on 3 December 2021.

**Supplementary Information:**

The online version contains supplementary material available at 10.1186/s13063-022-06487-3.

## Administrative information

Note: the numbers in curly brackets in this protocol refer to SPIRIT checklist item numbers. The order of the items has been modified to group similar items (see https://www.equator-network.org/reporting-guidelines/spirit-2013-statement-defining-standard-protocol-items-for-clinical-trials/).

Role of sponsor {5c}	The sponsor has ultimate responsibility for the initiation, management (or arranging the initiation and management) and/or financing (or arranging the financing) for the SENIOR study. The sponsor takes primary responsibility that the design of the SENIOR study meets appropriate standards and that arrangements are in place to ensure appropriate conduct and reporting.

## Introduction

### Background and rationale {6a}

Poor oral health, including dental caries and periodontal disease, is a very common problem for older adults residing in care homes and the issue is increasingly becoming a significant public health problem [1, 2]. Amongst older adults, 40% of the 75–84 age group and 33% of the 85 + age group have dental caries, whilst periodontal disease affects 69% of those over 65 years of age [3]. The oral health of care home residents is much worse than their community living peers. With increasing dependency, the ability for self-care deteriorates, poly-pharmacy leads to dry mouth and diets become rich in sugars [4]. All these factors significantly increase residents’ disease burden and the risk of future problems. Oral conditions impact on their quality of life, self-esteem, general health and diet, exacerbating underlying medical conditions [4–7]. Income-related inequality in oral health of older adults is also a major issue [8, 9].

Despite this high level of need, dental service provision in residential care is poor, with little emphasis on prevention [10, 11]. Access to domiciliary services is difficult and unscheduled care for dental problems (including hospital admissions) is common, complex to deliver and expensive [12, 13]. The World Health Organization (WHO) argue that the design of long-term care systems that are fit for ageing populations should take priority [14] and the Royal College of Surgeons of England (RCS) [15], Public Health England (PHE) [11] and the National Institute of Clinical Excellence (NICE NG48) [16] have all called for more high-quality research. Recently, the Care Quality Commission (CQC) have also highlighted the paucity of dental care in care homes in their Oral Health Care in Care Homes report published in June 2019 [17].

There is increasing evidence that Dental Care Professionals (DCPs) offer an alternative to using dentists to meet the future challenges in dental public health [18, 19]. DCPs are a broad range of professionals, which include dental therapists (DTs) and dental nurses (DNs). Previous research has demonstrated that DTs can identify and screen for dental caries and periodontal disease and are safe as front-line health care workers [20–22]. The feasibility, productivity and effectiveness of using DTs has been tested in primary care [21, 23, 24], but little has been undertaken in a care home environment. Emerging evidence suggests that the use of DCPs (DTs and DNs) within care homes has the potential to improve preventive advice, the provision of care and access to services [25].

Following a retrospective analysis of the 2010 Welsh dental care home survey data, Monaghan & Morgan [26] concluded ‘a large proportion of need in care homes could be wholly provided by hygienists or therapists’ and an ‘efficiency gain of direct access arises from individuals who do not need to see a dentist for any aspects of their care’. It is also argued that DTs can lead examinations in care home settings [27]. However, robust empirical evidence from definitive trials about how best to successfully implement and sustain DCP interventions within care home environments is currently lacking.

The aim of this study is to determine whether DCPs could reduce plaque levels (improve the oral cleanliness) of dentate older adults (over 65 years of age) residing in care homes over a 6-month period, when compared to ‘treatment as usual’ (commonly a reactive and ad hoc service provided by dentists), and also to determine whether this effect is sustainable over a further 6-month follow-up period.

### Objectives {7}

The objectives of the study are to:Undertake a cluster-randomised controlled trial (RCT) across Wales, Northern Ireland and England to determine whether role-substitution using DCPs could reduce plaque levels (improve oral cleanliness) of dentate older adults residing in care homes over a 6-month period, when compared to ‘treatment as usual’;Follow residents for a further 6 months to determine whether this effect is sustainable;Use semi-structured interviews to undertake a process evaluation of the trial to determine acceptability, treatment fidelity and pathways-to-impact with the following stakeholders (detailed in a parallel paper):Managers and staff of care homes to assess the intervention’s feasibility and sustainability;Residents, relatives and informal carers to explore the intervention’s acceptability;Managers and residents that refused participation to explore their narrative; andCommissioners of care renew care-pathways and pathways-to-impact; andUndertake a parallel cost-effectiveness analysis from a National Health Service (NHS) perspective.

### Trial design {8}

This is a multi-centre, two-armed, cluster-randomised trial, based on a superiority design, to determine whether DCPs could reduce levels of dental plaque of dentate older adults residing in care homes over a 6-month period, when compared with ‘treatment as usual’. Residents will be followed for a further 6 months to determine whether this effect is sustainable. Care homes (*n* = 40) will be randomised based on a 1:1 ratio (20 intervention and 20 control), with an average of seven residents recruited in each care home resulting in an estimated sample size of 280. Figure 1 provides an overview of the RCT’s design.

**Fig. 1 Fig1:**
[figure not shown]
SENIOR trial flowchart

A cost-effectiveness analysis from a NHS perspective will examine the potential long-term costs and benefits of the intervention.

A process evaluation involving semi-structured interviews with key stakeholders will be undertaken alongside the trial to explore the intervention’s acceptability and treatment fidelity (subject of an additional paper). It will also capture the contextual factors that shape the intervention, mechanisms that sustain or potentiate effects, unexpected pathways and consequences and the contextual factors that shape implementation. A semi-structured interview schedule will be developed in collaboration with the patient and public involvement (PPI) group. Audio-taped interviews will be conducted both in person and using virtual technology. Data will be anonymised, fully transcribed and analysed by the researchers using thematic analysis.

## Methods: participants, interventions and outcomes

### Study setting {9}

The trial will be conducted in 40 care homes from across Wales, Northern Ireland and England (London and North England). Further information about recruitment and randomisation of care homes is presented in the relevant sections below. DTs and DNs employed by the Community Dental Service (CDS) in each region will deliver the oral health intervention. CDSs are charged with the responsibility of providing NHS service provision for care homes on a regional basis.

### Eligibility criteria {10}

#### Selection of care homes

##### Inclusion criteria

Minimum of ten residents aged 65 years and over.

##### Exclusion criteria

(2)Current participation in TOPIC (Improving the oral health of older people in care homes) [28], Gwên am Byth [29] or another oral health programme; and(3)Care homes that only specialise in end−of−life or palliative care.

#### Selection of residents

Care home residents will be eligible to participate if they are able to meet the following inclusion criteria and have the capacity to provide consent:65 years and over;Dentate or partially dentate (at least six natural teeth); andFull−time resident in care facility.Exclusion criteria:Residents who are only receiving end−of−life or palliative care.

### Who will take informed consent? {26a}

The local study team at each study site will obtain written informed consent from eligible care homes and eligible residents. Care homes and their residents interested in taking part in the RCT will be given a Participant Information Sheet (PIS) and an Informed consent Form (ICF). Written informed consent will be taken at least 48 h after informing the care homes and their residents about the study. As the project involves sites in Wales, to comply with the Welsh Language Act 1993, the relevant PISs and ICFs will be translated into Welsh and offered bilingually.

On entry into the study, the local study team will complete a Six-item Cognitive Impairment Test (6-CIT) [30] with residents in order to assess their level of cognitive function. Residents will be asked to consent for the 6-CIT screen and for the results to be fed back to the care home manager to discharge our duty of care.

Consent into the study will follow guidance laid down within the Mental Capacity Act 2005. Potential participants will be assumed as having capacity to consent for themselves unless formally assessed as lacking capacity, in which case the views of a Personal Consultee (usually a relative) will be sought. If no Personal Consultee can be identified, a Professional Consultee who is (a) independent of the study and (b) knows the participant well enough to consider their views will be approached. If the participant’s lack of capacity is considered temporary, capacity will be reassessed prior to each contact with the researcher. If a participant communicates his/her objection to a research assessment or intervention, either verbally or non-verbally, the intervention will cease immediately. Further attempts will be made at a later time; however, if the participant continues to object then he/she will be withdrawn from the study. The safety and well-being of residents will be paramount at all times.

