### Criteria for discontinuing or modifying allocated interventions {11b}

Care homes and residents will be able to withdraw at any time during the study. Where possible, in agreement with participants, data from those withdrawn will be used in analysis unless consent for this is specifically withdrawn.

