**Fig. 2 Fig2:**
[figure not shown]
Time schedule of enrolment, interventions, assessments and visits for participants

The care homes allocated to the intervention arm will be asked to implement the oral health intervention during the study period (12 months, *t*_0_ to *t*_2_), and the care homes allocated to the control arm will be asked to continue with routine practice during the same 12-month period. Assessments (intervention and control group) will be undertaken at baseline (*t*_0_), 6 months after baseline (*t*_1_) and 12 months after baseline (*t*_2_).

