### Methods in analysis to handle protocol non-adherence and any statistical methods to handle missing data {20c}

Analysis will be conducted on an intention to treat basis, and if required, a per-protocol analysis will be conducted as a sensitivity analysis. The aim is to minimise the amount of missing data, supported by the limited additional visits required by the participants. However, there is an expectation that some missing data will occur; predictors of missingness will be investigated and will be considered for inclusion in the models. Multiple imputation will be employed to address missing outcomes where appropriate. Test modelling and missing data assumptions via sensitivity analyses will be undertaken.

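### Continued objection to the intervention alone ends outcome follow-up, an avoidable loss of the primary outcome by a route open only in the intervention arm

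*Protocol article*

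**What the plan says.** Section {26a} of the protocol article names two triggers in one sentence: "If a participant communicates his/her objection to a research assessment or intervention, either verbally or non-verbally, the intervention will cease immediately". Further attempts follow later, and then "if the participant continues to object then he/she will be withdrawn from the study". The consequence is the same whichever trigger applied.

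Section {11b} allows homes and residents to withdraw at any time and adds: "Where possible, in agreement with participants, data from those withdrawn will be used in analysis unless consent for this is specifically withdrawn".

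The text after Fig. 2 in Participant timeline {13} puts the assessments in both arms: "Assessments (intervention and control group) will be undertaken at baseline", and again at 6 and 12 months. Control homes carry on with routine practice.

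The primary outcome ({12} and {14}) is whether a resident's mean plaque index has halved between baseline and 6 months, so it needs a 6-month examination.

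On analysis, {20c} states: "Analysis will be conducted on an intention to treat basis, and if required, a per-protocol analysis will be conducted as a sensitivity analysis"; {20a} says the same. On gaps in the data, {20c} adds: "Multiple imputation will be employed to address missing outcomes where appropriate", together with a search for predictors of missingness and sensitivity analyses of the missing-data assumptions.

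No section describes a resident who stops the intervention and stays in follow-up. The retention section {18b} deals with contact with the homes.

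**The concern.** An intention-to-treat comparison needs outcomes from residents who did not take up their allocated treatment. Section {26a} ends follow-up for some of those residents because they did not take it up, even where they would have allowed the 6-month examination.

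The two arms are not equally exposed to this. Objection to an assessment can arise in either arm. Objection to the intervention can arise only where there is one: therapist visits, nurse visits and professionally applied varnish under {11a}.

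If residents who persistently refuse oral care are also less likely to halve their plaque, losing their outcomes from one arm moves the primary result towards the effect among those who accept treatment.

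**Working it through.** **1. The plan's own figures.** Inputs from {14}: success 0.10 in control and 0.29 in intervention, 20 homes per arm, 5 completers per home, intraclass correlation 0.05, attrition 28%, 5% significance (two-sided assumed).
- Design effect: 1 + (5 − 1) × 0.05 = 1.20. Effective size per arm: 100 / 1.20 = 83.3.
- Total recruited: 200 / 0.72 = 278, against 280 stated.
- Power with unpooled variance: 89.0%, against 90% stated.

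The planning figures reproduce closely. They do not decide this point, because the 28% is not split by arm or by reason.

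**2. What happens to a resident who refuses only the intervention, rule by rule.**
- {26a}: continued objection leads to withdrawal from the study.
- {11b}: data already held may be used. Before 6 months that means baseline data. A later examination is not provided for.
- {12} and {14}: without a 6-month plaque score there is no primary outcome.
- {20a} and {20c}: the resident belongs to the intention-to-treat population with a missing outcome.

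**3. Illustration of size.** The protocol gives no refusal rate, so these inputs are assumptions. Let f be the fraction of the intervention arm lost this way, r the success rate those residents would have had, and 0.29 v 0.10 the true rates among all randomised. Other losses are taken as unrelated to arm and outcome.

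Rate among intervention residents still examined = (0.29 − f × r) / (1 − f).

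| f | r = 0.10 | apparent difference | overstatement | r = 0 | apparent difference |
|---|---|---|---|---|---|
| 5% | 0.285 / 0.95 = 0.300 | 0.200 | 0.010 (5%) | 0.305 | 0.205 |
| 10% | 0.280 / 0.90 = 0.311 | 0.211 | 0.021 (11%) | 0.322 | 0.222 |
| 20% | 0.270 / 0.80 = 0.3375 | 0.2375 | 0.0475 (25%) | 0.3625 | 0.2625 |

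The overstatement equals f × (0.29 − r) / (1 − f). It is zero when r = 0.29, that is, when refusers would respond like accepters.

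**4. If there is no true effect.** Take 0.10 in both arms and r = 0, the extreme case. The rate among intervention residents still examined is 0.10 / (1 − f). With the design effect applied, the two-sided rejection rate is about 5.1% at f = 5%, 5.6% at 10% and 7.8% at 20%, against a nominal 5%.

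**5. Does imputation repair it?** Take f = 10% and r = 0.10. If refusers are imputed from similar accepters, the arm's rate is 0.90 × 0.311 + 0.10 × 0.311 = 0.311. The true value is 0.90 × 0.311 + 0.10 × 0.10 = 0.29. Predictors such as baseline plaque or cognition may close part of the gap. Refusal itself cannot be estimated as a predictor if those who refused have no 6-month scores; any shift for them has to be assumed.

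**The case against.** The case on the other side has real weight.

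- **The analysis set.** A reader might infer that refusers are removed from the analysis, or that intention to treat is abandoned. The document says neither. Section {11b} states that "data from those withdrawn will be used in analysis unless consent for this is specifically withdrawn", and {20c} plans imputation, predictors of missingness and sensitivity analyses. A missing outcome with a missing-data plan does not contradict an intention-to-treat declaration. The imputation model belongs in an analysis plan that is not shown. This stands: the defect is an uncollected outcome, not an exclusion.
- **The balance between arms.** A reader might infer that the rule acts mainly on the intervention arm. Every resident in both arms also faces examinations with probing and questionnaires, and those who object to oral procedures may object to these too. Much of the intervention also works through staff. The extra trigger in one arm is a matter of design; how often it would be used is not stated.
- **Purpose and context.** The sentence is a safeguard within the Mental Capacity Act paragraph, and it requires further attempts before withdrawal. Entry is limited elsewhere ({10}, {18a}) to residents able to consent, although {26a} also describes a consultee route. A single refused application does not trigger withdrawal. The fuller protocol may separate levels of withdrawal. None of this changes the current wording, which gives one consequence for two different objections.
- **The figures.** They assume no matching loss in control, that every refuser would have accepted the examination, and no correction from covariates. They are an upper illustration for each refusal rate and value of r.

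What survives is narrower but firm: a score that could have been collected is not collected, by a route that exists in one arm only.

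**Conclusion.** The point holds as a moderate one. As written, {26a} ends outcome collection for an intervention resident who keeps objecting to the intervention, even if that resident would accept examination. Neither {11b} nor {20c} replaces the missing 6-month score. The result is an avoidable loss of the primary outcome that can differ by arm and may not be at random.

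The documents do not support a statement that the primary result will be inflated by a known amount. The overstatement of 5% to 25% of the planned difference rests on assumed refusal of 5% to 20% and on refusers succeeding at 0.10. It would be larger if they succeeded less often and zero if they responded like accepters. At 5% to 10% refusal, the effect on the false-positive rate is small even in the extreme case. The reason to act is that the loss is cheap to prevent and cannot be undone at the analysis stage.

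**What to change.** Reconcile {26a}, {11b} and {20a}/{20c} on one question: does objection to the intervention alone end outcome follow-up?

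- Leave unchanged that the intervention ceases on objection, and the resident's right to refuse assessments or to withdraw.
- State that a resident who objects only to the intervention stays in the study and is still offered the scheduled 6- and 12-month assessments.
- Reserve withdrawal from the study for continued objection to the assessments or withdrawal of consent.
- Record which of the two was refused, and report it by arm.

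**Cost.** A protocol amendment and a field on the withdrawal form. The information sheet and consent form may need to change, with notification of the ethics committee, because residents who have objected would still be approached for assessments. No visits are added. The expected effect becomes slightly smaller than among accepters alone, and residents who also decline examination will still be missing. The article reports the trial as not yet recruiting, so the change could be made before any resident is affected.

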### Additional consent provisions for collection and use of participant data and biological specimens {26b}

Not applicable as no biological specimens will be collected as part of this trial.

## Interventions

### Explanation for the choice of comparators {6b}

The control will be routine practice. The results from a PHE survey [10] and a Priority Setting Partnership exercise undertaken with four stakeholder groups, including service users, carers, third sector organisations and oral health specialists [31], suggest that this practice is likely to be heterogeneous and ad hoc, including intermittent domiciliary care and infrequent tooth-brushing with toothpaste by unsupervised residents.

